### Development of RAW-PA

To inform the development of the current intervention using participatory research principles, the research team piloted the feasibility, usability and acceptability of the Fitbit® Flex and accompanying app/web-based portal in 60 Year 8 adolescents (aged 13–14 years; 100% response rate) from three secondary schools (one low, one mid and one high socio-economic status (SES)) in Melbourne. As there is a dearth of information concerning the feasibility of these devices in adolescents [28], exploring the experiences of adolescents from different SES areas provided insights into whether these technologies offer promise for promoting physical activity levels among adolescents with a range of socioeconomic circumstances.

The Fitbit® was selected as it accounts for a large proportion of activity tracker sales [45], performs well in comparison to research grade monitors [46], and the accompanying app is free to use. Students wore the Fitbit® Flex for six weeks and completed three surveys at the end of Weeks 1, 3 and 5. After Week 6, students were interviewed regarding their thoughts about activity trackers and how to integrate such technologies into a physical activity intervention. Adolescents were asked to provide feedback about how the program should be delivered (e.g. style, frequency), the format and content of the digital (internet-based) resources, and strategies for facilitating engagement and motivation during the intervention was sought. Adolescents generally reported that the Fitbit® was easy to use (97% agreed at Week 1, 100% agreed at Weeks 3 and 5), over 80% wore the Fitbit® on any given day, the Fitbit® was used regularly to track daily activity (over 70% at each time point checked their activity ≥2 times a day), and their awareness of their activity levels (≥90% week 1) and intentions to be more active increased (≥80% at week 1) as a result of the Fitbit®. However, adolescents also indicated that wearing an activity tracker (alone) may not be enough to increase activity levels (≥40% agreed in week 1, ≥50% week 5). RAW-PA was subsequently developed based on the adolescents’ feedback, and suggestions about the content and presentation of the resources were reviewed by the adolescents and refined further.

### Measures

Research assistants will conduct all student assessments in schools. Parents will complete surveys at home. To ensure consistency between research assistants, a protocols document has been developed for use at all data collections and all research staff will undergo a training session prior to assessments. A range of measures are described below and will be collected at baseline, post-intervention and at 6-months post-intervention, unless otherwise stated.

### Physical activity and sedentary time

#### Accelerometry

Physical activity and sedentary time will be objectively-assessed using hip-mounted ActiGraph accelerometers (model GT3X+; ActiGraph, Pensacola, FL, USA). Students will be instructed to wear the accelerometer for 8 consecutive days at each time point during waking hours (except during water-based activities). The ActiGraph is the most commonly used accelerometer in youth research [47] and has acceptable validity and reliability for assessing adolescents’ free-living activity levels [48]. Raw acceleration data will be sampled, downloaded and processed into 15 s epochs using manufacturer proprietary software. Age-specific thresholds will be used to determine time spent in moderate— and vigorous-intensity physical activity [49]. Moderate— and vigorous-intensity physical activity will be summed to determine time spent in daily MVPA. Sedentary time will be defined as ≤100 cpm [50]. Time spent sedentary or physically active for the whole day and specific periods of the day (e.g. after school) will be obtained.

#### Survey measure

Activity levels will be assessed using a brief self-report measure that asks adolescents to report the number of days (0–7) they were physically active for a total of at least 60 min/day (1) over the past 7 days and (2) over a typical or usual week [51]. Responses to these items will be averaged for use in the analyses. This measure has been validated for use with Australian adolescents [52].

#### Leisure-time physical activity and sedentary behaviours

Adolescents’ leisure-time behaviours will be assessed using items adapted from the validated Middle-School Physical Activity and Nutrition (M-SPAN) Survey [53]. Students will be asked how much time they spend in leisure-time sedentary behaviours such as watching television, using the internet and doing homework, using a 6-point scale ranging from none to 4+ hours/day on weekdays and weekends. Usual mode of transport to and from school will also be assessed using an adapted measure from a survey developed by Timperio and colleagues [54]. Students will be asked to report the main method of transport (i.e., walked, cycled, car, public transport) to school and from school each weekday.

### Mediators of behaviour change

As noted above, this study will also examine potential mediators of behaviour change. Few interventions examine potential mediators, even those based on behaviour change theory, despite the potential for such information to provide insights into why an intervention may or may not be efficacious [55]. The following potential mediators of behaviour change will be examined as they have been examined previously in children [56, 57] and adolescents [58, 59], and they are being specifically targeted through the 12-week program via the weekly missions (see Table 2).

#### Self-efficacy

Self-efficacy will be assessed using five items from an existing scale that has acceptable validity and reliability in young adolescents [60]. Students will respond to each question using a 6-point Likert-type scale, with responses ranging from disagree a lot (1) to agree a lot (6).

#### Social support

Social support from friends and family will be assessed using nine items from a previously validated measure that asks students to respond to items on a 5-point Likert-type scale ranging from never (1) to always (5). These items have acceptable reliability [60]. Social support from teachers will be assessed using 4 items adapted from the friends and family items and using the same response scale as reported above. Questions include “… did your teachers encourage you to be physically active during recess or lunch breaks?” and “…did you teachers organise physical activity or sport for you?”

#### Behavioural strategies

Six previously validated items will be used to assess social-cognitive strategies for engaging in physical activity [60]. Students will respond to each item using a 5-point Likert-type scale ranging from never (1) to always (5). These items have acceptable test-retest reliability in adolescents [60].

#### Barriers to physical activity

Perceived barriers to physical activity will be assessed using nine items drawn from the Adolescent Physical Activity Perceived Barriers and Benefits Scales [61]. Students will respond to each item using a 4-point Likert-type scale ranging from ‘not at all true’ (1) to ‘very true’ (4). Items include “I am too busy” and “It is very hard work”. The perceived barriers scale has acceptable test-retest reliability and internal consistency [61].

#### Enjoyment

Enjoyment of physical activity will be assessed using the 16 item Physical Activity Enjoyment Scale (PACES; [62]). Students will be asked the extent to which they agree with each item (e.g. ‘I enjoy it’, ‘I dislike it’ etc.) using a 5 point Likert-type scale ranging from disagree a lot (1) to agree a lot (5). PACES has been validated for use with adolescents [62].

### Covariates

#### Anthropometry

Body mass will be measured to the nearest 0.1 kg using a calibrated electronic scale (Tanita BC-351; Tanita, Japan). Stature will be measured to the nearest 0.1 cm using SECA portable stadiometers (model 217; SECA, Germany). Waist circumference will be measured using a flexible steel tape at the narrowest point between the bottom rib and the iliac crest, in the midaxillary plane. Two measurements of body mass, stature and waist circumference will be taken and, in the event of a discrepancy over 0.1 kg or 1 cm, a third measure will be taken. The average of the two acceptable measures will be reported. Body mass index (weight/stature^2^, kg/m^2^) will also be calculated.

#### Demographics

Parents will be asked to complete a short survey that collects demographic data about the family (e.g. parent education level, employment status, marital status etc.) at baseline.

### Process evaluation feasibility measures

A range of process data will be collected to complement the outcome data collected during the study. Process data will be collected to assess the fidelity, feasibility, acceptability and appeal of RAW-PA. All process data collected will follow current process evaluation guidelines [63].

#### Feasibility/acceptability/appeal

The adolescents’ engagement with the social media intervention components will be documented (e.g. numbers reporting engagement with the resources, completion of weekly ‘missions’ or ‘challenges’, information posted by participants, Facebook ‘likes’ and comments etc.). Use of the Fitbit® throughout the 12 weeks (including missing days/syncing of data) will be collected via Fitabase (www.fitabase.com), a commercially-available platform for collecting these data from multiple users. At post-test, adolescents will complete a process evaluation questionnaire about the length of the intervention, their enjoyment and use of the different intervention components, and how they think the program could be improved. Qualitative data will be collected from adolescents (focus groups of 7–8 students per group) and school teachers (interviews) to examine the feasibility and appeal of the intervention from a participant’s and organisation’s perspective, respectively.

#### Fidelity

Data collected will include the number of text messages and emails sent by the research team, and the number of Facebook posts by the research team.

### Data analysis

The analysis of the quantitative primary and secondary outcomes will be conducted in Stata (StataCorp LP, College Station, Texas). Multilevel modelling will be used as these analyses are appropriate for the analysis of clustered data (adolescents, schools) and can handle missing data [64]. The models will assess the impact of RAW-PA (intervention, control) and adjust for potential confounders (e.g. monitor wear time, sex). Potential mediating effects will also be explored using the product-of-coefficients test of MacKinnon and colleagues [65]. Descriptive analyses will be used to examine the feasibility/acceptability/appeal of the intervention components of the study. Qualitative data from participant focus groups and teacher interviews will be analysed thematically using a mixed analysis procedure using content analysis and verbatim quotes [66].

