### Sample size

Previous population-based studies were used to estimate the SD of mean daily minutes of MVPA (18.6 [37]) and the intraclass correlation coefficient for clustering within schools (ICC; 0.01 [38]). Based on an initial sample size of 300 adolescents (150 per study arm) participating from 12 schools (25 students per school), the z-statistic for 80% power is 0.84 and the z-statistic for α = 0.05 is 1.96. Based on 70% providing usable data at post-intervention, it was estimated that there would be 210 students (105 per arm) at post-intervention. With this sample size, the study is able to detect a difference in the mean daily MVPA between intervention and control students of 7.9 min at post-test.

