### Blinding and randomisation

In this cluster-RCT, recruitment and baseline data collection will be conducted prior to randomisation. Schools will be match-paired based on their size and SEIFA score and randomly allocated to either the intervention (6 schools) or wait-list control (6 schools) group by a computer-based random number generator. Randomisation will be conducted by an independent researcher not involved in the current study. Participants attending schools randomised to the intervention group will commence the program once baseline measures have been completed for all participants. Participants in the wait-list control group will be provided access to the intervention materials after the completion of the 6-month follow-up assessments.

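### With 12 randomised schools, planning rests on normal quantiles and the analysis paragraph gives no small-sample provision: 7.9 min has about 70–73% power on 10 df, and a z-referenced test would run above 5% if the ICC exceeds 0.01

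*Protocol article*

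**What the plan says.** Three sections of the protocol article bear on this.

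- **Blinding and randomisation.** Schools are paired on size and SEIFA score and then "randomly allocated to either the intervention (6 schools) or wait-list control (6 schools) group". An unpaired arm comparison therefore has 12 − 2 = 10 between-school degrees of freedom, and a pair-level comparison has 6 − 1 = 5.
- **Sample size.** The calculation uses normal quantiles: "the z-statistic for 80% power is 0.84 and the z-statistic for α = 0.05 is 1.96". It gives a detectable difference of 7.9 min of daily MVPA with 105 students analysed per arm.
- **Data analysis.** The models will be fitted in Stata, with adjustment for variables such as wear time and sex. On clustering it says "Multilevel modelling will be used as these analyses are appropriate for the analysis of clustered data (adolescents, schools"). It names no estimator, reference distribution or degrees-of-freedom method.

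**The concern.** A school random intercept models the correlation between students in the same school. It does not by itself allow for the school variance being estimated from only 12 units. If the estimated arm effect is divided by its standard error and compared with 1.96, that uncertainty is ignored. ML adds to the problem because it biases the school variance downwards. The only inferential scale the article commits to is the normal one.

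Two things are at stake. The first is whether the primary test and its confidence interval hold their nominal levels, given that 12 schools cannot confirm that the ICC is as low as 0.01. The second does not depend on how the final model is fitted: the published power figure assumes a reference distribution that a valid analysis of 12 schools would not use.

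**Working it through.** **Inputs, all from Sample size and from Blinding and randomisation:** "SD of mean daily minutes of MVPA (18.6 [37"]); "intraclass correlation coefficient for clustering within schools (ICC; 0.01 [38"]); "300 adolescents (150 per study arm) participating from 12 schools (25 students per school"); "Based on 70% providing usable data at post-intervention", which gives 105 per arm and 25 × 0.7 = 17.5 per school; six schools per arm.

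**Step 1. Reproduce the 7.9 min.** Detectable difference = (1.96 + 0.84) × SE, with SE = 18.6 × √(2 × DE / 105) and DE = 1 + (m − 1) × 0.01.

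- m = 17.5: DE = 1.165, SE = 2.771, difference = 7.76 min.
- m = 25: DE = 1.24, SE = 2.859, difference = 8.00 min.
- No clustering: DE = 1, SE = 2.567, difference = 7.19 min, which does not match.

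The stated 7.9 lies between the two clustered values. It is reproduced to within rounding and the choice of m, on normal quantiles.

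**Step 2. The same calculation on t.** The 97.5% point of t on 10 df is 2.228, which is 1.137 times 1.96. Power is P(T > critical value) for a noncentral t with noncentrality 7.9 / SE, that is 2.851 (DE 1.165) or 2.764 (DE 1.24).

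| Reference | Power at 7.9 min | Difference for 80% power |
|---|---|---|
| z, DE 1.165 / 1.24 | 81% / 79% | 7.76 / 8.00 min |
| t, 10 df, DE 1.165 / 1.24 | 73% / 70% | 8.6 / 8.9 min |
| t, 5 df, DE 1.165 / 1.24 | 63% / 60% | 9.7 / 10.0 min |

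The 5 df row is a pair-level analysis that assumes no gain in precision from matching. Any gain would offset part of the loss.

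**Step 3. Type I error if z is the reference.** The simulation used 400,000 null trials per ICC, 6 versus 6 schools of 17.5 students, no covariates, and a random-intercept model fitted in closed form with the school variance truncated at zero. The test rejects when |estimate / SE| > 1.96. Only ICC 0.01 comes from the article; the other values are assumptions.

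| ICC | ML, z | REML, z |
|---|---|---|
| 0.01 | 6.0% | 5.0% |
| 0.02 | 6.9% | 5.7% |
| 0.03 | 7.8% | 6.3% |
| 0.05 | 8.9% | 7.0% |
| 0.10 | 10.0% | 7.7% |

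The inflation is small at 0.01 because the school variance is estimated as zero in 57% (ML) or 42% (REML) of null trials. The standard error then comes from the pooled variance. When truncation becomes rare, the limits are 10.4% for ML and 7.8% for REML. A t-test on school means with 10 df holds 5.0% at every ICC.

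**Step 4. Check the remedy.** The same simulation was run for REML with Satterthwaite-type df: 10 when the school variance is positive, residual df when it is zero. Type I error is 4.0% at ICC 0.01, rising to 5.0% at 0.10. Forcing 10 df in every trial is more conservative, at 2.7% for ICC 0.01.

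**The case against.** The strongest reply is that the article never says it will use ML, z-tests or default settings. A reader might infer from the mention of Stata, together with the 1.96 in Sample size, that z-based testing is planned and that the primary test therefore exceeds 5%. The documents do not support that. Naming a package fixes neither estimator nor reference distribution. Normal quantiles in a planning formula do not bind the final model. A condensed article may leave the degrees-of-freedom method to an analysis plan that is not shown. It is also correct that multilevel models suit clustered data. All of this stands, so the type I error result must be conditional.

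It also stands that inflation at the protocol's own ICC is about one percentage point with ML and nil with REML. Clear inflation needs an ICC above about 0.02 to 0.03, which is outside anything the article gives. The remedy has a price, and matching complicates it: the unpaired 10 df is not the only candidate.

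The reply does not remove the sample-size result. The normal quantiles are stated there and they produce the 7.9 min. If the final analysis is valid for 12 schools, the stated power is too high. If it follows the planning scale, its error rate is not secured once the ICC exceeds the planning value. The two sections need to be put on one basis in either case.

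**Conclusion.** The point holds in a conditional form for the test and unconditionally for the planning figure.

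- **Power.** The 7.9 min difference has about 70–73% power on t with 10 df, not 80%. The 80% detectable difference is about 8.6–8.9 min. This takes the article's SD, ICC and retention as given, with equal school sizes and no covariates.
- **Type I error, if z is used.** It is about 6% (ML) or 5% (REML) at ICC 0.01, and about 8–10% or 6–8% at an assumed ICC of 0.03–0.10. For the same standard error, a 1.96-based interval is about 12% narrower than one on 10 df (1.96 / 2.228 = 0.88).

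This does not show that the primary analysis is invalid. It shows that the only scale stated is the wrong one for 12 schools, and that the analysis paragraph does not correct it. It should be corrected before analysis. Covariate adjustment and unequal school sizes were not in the simulation and would move the figures somewhat.

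**What to change.** 1. In Data analysis or the statistical analysis plan, specify REML with Kenward-Roger or Satterthwaite degrees of freedom for every arm comparison, and take confidence intervals from the same reference distribution. The simulation covered a Satterthwaite-type rule; Kenward-Roger was not simulated separately.
2. Keep the school random intercept in the model whatever its estimated variance.
3. If a school-level t-test or permutation test is added as a check, make it respect the matching. A paired t-test has 5 df. Six pairs allow 2⁶ = 64 allocations, so the smallest two-sided permutation p-value is 2/64, about 0.031.
4. Restate Sample size on the chosen basis. With 10 df, report about 70–73% power at 7.9 min, or a detectable difference of about 8.6–8.9 min.

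The analysis change is one model option and leaves the design untouched. The costs are wider intervals (a critical value of 2.228 instead of 1.96 when 10 df apply), a slightly conservative test of about 4% if the ICC really is 0.01, and a less favourable published power figure.

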## Discussion

Physical activity is an integral component of a healthy lifestyle. However, as only 13% of 12–14 year olds in Australia currently engage in sufficient daily physical activity to benefit their health, there is a need for efficacious strategies to increase activity levels. This is particularly true for adolescents living in socioeconomically disadvantaged areas who are an underrepresented group in physical activity interventions [14]. This is despite the fact that disadvantage is linked with declines in physical activity during the teenage years [10] and a greater risk of poor health outcomes across the life course [9]. To date, only a small number of studies have delivered interventions specifically targeting adolescents living in socioeconomically disadvantaged areas, and limited effects on physical activity levels have been observed [15, 16, 18, 20, 67].

The aim of RAW-PA, a 12 week multicomponent intervention, is to examine the effectiveness of a wearable activity tracker combined with behaviour change resources to promote physical activity in inactive adolescents attending schools in socioeconomically disadvantaged areas. It intends to capitalise on the increasing pervasiveness, appeal, and rapid uptake of wearable activity trackers, and the opportunities these devices bring to physical activity and health promotion research. RAW-PA will provide insights into how such technologies are used by adolescents, addressing an important gap in the literature to date [68]. It will identify whether combining self-monitoring via the wearable activity tracker and the accompanying resources, which are designed to help students learn and develop key behaviour change techniques, will help the adolescents to change and maintain changes in active behaviours. Moreover, utilising individual and team ‘missions’, encouraging participants to share tips for increasing activity levels, and the focus on the accumulation of physical activity every day may address potential contextual barriers often faced by those from socioeconomically disadvantaged backgrounds, such as a lack of social support, financial constraints and safety concerns [14].

An important aspect of this study is that the potential applications of the research findings, including translation and broader dissemination, have been considered. The translational aspect is often an overlooked component of behaviour change programs [69, 70]. Firstly, whilst this trial is being evaluated in urban areas of Melbourne, the online delivery of the intervention facilitates potential reach into regional and rural areas. Secondly, the intervention is being delivered via a popular social media platform, highly accessed by adolescents, and has been designed to be flexible, readily accessible and interactive. This social element addresses a key motivator for physical activity in those from socioeconomically disadvantaged areas [14]. Thirdly, as mobile phone use and internet access is ubiquitous in Australia, including in disadvantaged areas [34], this study had the potential to address potential inequities in access to structured resources often experienced by adolescents living in disadvantaged areas [71]. Since inexpensive trackers are increasingly available and costs are continuing to decrease, this may facilitate accessibility to a broader range of consumers.

This study has some limitations. Due to the multicomponent nature of the study, the effect of each individual component will not be able to be determined; though it is possible to assess the appeal and perceived effectiveness of each component via process evaluation. Second, a specific wearable activity tracker – the Fitbit® Flex - will be used. As the wearable activity tracker market is highly competitive and new devices are constantly being produced and marketed, it is possible the Flex will be superseded or become obsolete over the course of the study. However, there is no reason why the findings from this study will not be generalisable to other high quality, low cost devices that are available or will likely become available in the future.

